## Abstract

**Background:**

Common mental disorders, such as depression, anxiety disorder, and adjustment disorder, have emerged as a major public and occupational health problem in many countries. These disorders can have severe consequences such as absenteeism and work disability. Different interventions have been developed to improve the return-to-work of employees with common mental disorders, but still a large proportion of employees experiences health and work problems after their return-to-work. For this reason, the SHARP-at work intervention is developed to prevent a relapse of sickness absence among employees who have returned to work after a period of sickness absence because of common mental disorders. We aim to evaluate the effectiveness, cost-benefit and process of the intervention compared to care as usual.

**Methods/Design:**

The study is designed as a cluster-randomised controlled trial with randomisation at the level of the occupational physician. Employees who have returned to work after a period of sickness absence because of a common mental disorder are included in the study. Employees in the intervention group will receive the SHARP-at work intervention. The intervention focusses on active guidance of employees by occupational physicians during the first weeks of work after sickness absence. Employees in the control group will receive care as usual. Outcomes will be assessed at baseline and at 3, 6, and 12 months follow-up. The primary outcome is cumulative recurrent sickness absence days. Secondary outcome measures are mental health, work functioning, and coping. Adherence to the protocol, communication between stakeholders, and satisfaction with the treatment are the process measures assessed in both study groups. Cost-benefit is calculated from a societal perspective. Finally, prognostic factors for a relapse of sickness absence are investigated.

**Discussion:**

This study goes beyond return-to-work by focussing on the prevention of recurrent sickness absence. The study incorporates not only outcomes on sickness absence and mental health but also on health-related work functioning. The results of this study can contribute to a further development of practice guidelines and the promotion of sustainable work participation.

**Trial registration:**

NTR1963

## Background

Common mental disorders (CMDs), such as depression, anxiety disorder, and adjustment disorder, have emerged as a major public and occupational health problem in many countries [1]. Several studies have found a relationship between CMDs and long term sickness absence and work disability [2-7]. In the Netherlands, about one in every three new work disability benefit recipients is disabled for work because of mental health problems [8,9]. The increase in sickness absence and work disability because of CMDs has serious negative economical consequences calling for preventive action [3,5,7,10,11].

Recently, attention is also given to the at-work decrements in performance because of CMDs, which seems to be even more costly than absenteeism [1,6,12-15]. In their review, Lerner and Henke show that depression is significantly associated with a reduction of job performance and productivity; it was demonstrated that employees with a significant improvement in depression still have more trouble with performing well compared to their healthy colleagues [6]. These findings emphasize the importance of interventions aiming at employees with CMDs who are at work. Yet, most interventions for employees with mental health problems are curative and focus on reintegration [16-20]. No interventions exist which aim at providing support after return-to-work although it is known that employees who return to work often are not fully recovered from their initial complaints [18-20]. Moreover, research in the Netherlands showed that one out of five employees who have returned to work after a sickness absence period because of a CMD experiences a relapse of sickness absence due to CMDs (Koopmans et al., submitted for publication). For these reasons, we have developed an intervention aiming at the prevention of a relapse of sickness absence among employees who have (partially/fully) returned to work after a period of sickness absence because of a CMD.

The intervention is called "SHARP-at work". SHARP is an acronym for Stimulating Healthy participation And Relapse Prevention. The intervention is based on the guideline "Management of mental health problems of workers by occupational physicians" of the Netherlands Society of Occupational Medicine. This evidence-based guideline, developed in 2000 and revised in 2007, is introduced to facilitate the return-to-work of employees on sickness absence because of mental health problems [21,22]. The goal of the guideline is to activate the employee when stagnation occurs in the process of problem identification, problem solving, and implementation of solutions regarding issues that caused sickness absence and factors that hinder return-to-work. By this, employees learn to control their own recovery. The guideline has shown to be effective in reducing the number of employees who are on long-term sickness absence because of CMDs [18,23,24].

The SHARP-at work intervention is developed to improve problem solving strategies regarding problems or opportunities at work for employees who have returned to work. Successful implementation of solutions is stimulated by guiding employees in involving their line manager (i.e. the supervisor). This intervention will be implemented by the occupational physicians (OPs) of the employees. The goal of the intervention is the prevention of a relapse of sickness absence and improving mental health and work functioning.

Given the serious consequences of CMDs for the individual employee and the high social and economic costs for the workplace, the employer, the health system, and society, the promotion of sustainable work participation among employees with CMDs is very important. Therefore, the primary aim of this study is to evaluate the effectiveness of the SHARP-at work intervention compared to care as usual (CAU) in preventing a relapse of sickness absence among employees who have returned to work after a period of sickness absence because of a CMD. We hypothesise that employees who return to work, after sickness absence because of a CMD, and undergo the SHARP-at work intervention will have less recurrent sickness absence days compared to employees who receive CAU. Secondary aims are to improve mental health and work functioning and to stimulate better coping mechanisms. In addition, the cost-benefit of the intervention will be examined. Along with these evaluations, we will conduct a process evaluation among employees, OPs, and line managers. Finally, prognostic factors for a relapse of sickness absence will be investigated. To our knowledge, this is the first study focussing on guiding employees at work after they have returned to work because of a period of sickness absence due to CMDs.

## Methods/Design

The CONSORT statement and the extension for cluster randomised trials is used to describe the design of the study [25,26].

### Study context

In the Netherlands, both the employer and the employee are responsible for return-to-work. According to the Dutch Gate Keeper Act, the employer has a two-year obligation to pay an employee on sickness absence. After this period, the employee can apply for work disability benefit. During the first two years of sickness absence, the employer and the employee have to make all efforts possible to realise a return-to-work for the employee. For this reason, the employer is obliged to contract an occupational physician (OP). The employee has to visit the OP when being on sickness absence. OPs treat employees according to guidelines. For CMDs, the evidence-based guideline of the Netherlands Society of Occupational Medicine is used to support employees on sickness absence because of mental health problems [21,22]. The OP and the employee should be meeting each other regularly as long as the employee has not fully returned to work. After full return-to-work, at least one meeting should take place to focus on relapse prevention. In practice, OPs do not seem to act upon this last step of the guideline (Rebergen et al., submitted for publication).

### Study design

The study is designed as a two-armed cluster-randomised controlled trial for the prevention of a relapse of sickness absence by the SHARP-at work intervention compared to CAU (Figure 1). The study is conducted among employees who have returned to work after a period of sickness absence because of a CMD. Randomisation occurs at the level of the OP because employees can not be randomly assigned to OPs and OPs can not be expected to provide both guidance according to the SHARP-at work intervention and CAU. OPs, who have given their consent for participation, are randomised in the intervention or control group. OPs in the intervention group receive training in the SHARP-at work intervention. OPs in the control condition do not receive this training until the end of the study period and provide CAU.

**Figure 1 F1:**
[figure not shown]
**Study design**.

Employees will be included from December 2009 to December 2010. OPs will invite an employee to participate in the study if the employee is diagnosed with a CMD at the start of the sickness absence period and ready to return to work. Employees treated by an OP trained in the intervention will receive the intervention. Employees who are treated by an OP in the control group will receive CAU. Regardless of the treatment group, employees still have the possibility to be treated simultaneously by other health care workers.

The Medical Ethical Board of the University Medical Center Groningen has given approval for the study design, the research protocol, questionnaires, information letters, and the informed consent. Employees can participate voluntarily in this study. They are informed that they can leave the study at any time without consequences. All employees sign an informed consent. If an employee drops out, care will be continued.

### Recruitment of occupational physicians

Recruitment of OPs takes place in collaboration with ArboNed, one of the largest Occupational Health Services (OHS) in the Netherlands. OPs participating in this study are employed at this OHS and are affiliated with companies of different sizes, in different sectors and in different parts of the Netherlands. Company size ranges from less than five employees up to more than a 1000 employees in different sectors, for instance industry, education, health care, and customer services. All regions in the Netherlands, except the south, are participating in the study. OPs are excluded when they: 1. have an upcoming retirement, resignation, sabbatical, or pregnancy leave, or 2. are unable to use the internet and/or email.

### Recruitment of participants

#### Inclusion criteria

Employees participating in the study are between 18 and 63 years old and employed in a paid job. Furthermore, they have: 1. a diagnosis of a CMD given by their OP at the start of the sickness absence period, 2. a period of sickness absence due to a CMD of at least two weeks, and 3. a planned return-to-work within two weeks.

#### Exclusion criteria

Employees are excluded when: 1. the present sickness absence spell has been longer than 12 months, 2. they have had a period of sickness absence due to a CMD three months prior to the present sickness absence spell, 3. they have severe mental disorders, like psychotic disorders, bipolar disorder, or post-traumatic stress disorder, 4. they have somatic complaints or disorders that have a predominant influence on work disability, 5. they are pregnant or have an upcoming retirement, resignation, or layoff, and 6. they are unable to speak, read, write, or understand the Dutch language.

#### Procedure

Employees are recruited by the OPs participating in the study. The OP checks all inclusion and exclusion criteria. The diagnosis of a CMD has been made by the OP at the start of the sickness absence period. OPs are trained in diagnosing mental disorders and use a nationwide coding system, Classification of Diseases (in Dutch: CAS) [27], based on the International Classification of Diseases [28].

If the employee is interested to participate in the study, the OP asks whether contact information of the employee can be given to the researcher (IA) and hands over an information folder about the study. After the employee has received the information and has given approval for the researcher to make contact, the OP gives the contact information to the researcher. The researcher contacts the employee and asks if the employee would like to participate in the study. If the employee is willing to participate, informed consent and the baseline questionnaire (electronic or paper version) are send to the employee with a postage paid envelope.

When the informed consent and the baseline questionnaire are filled in and returned to the researcher, OPs in the intervention group are informed that the intervention can be started. OPs in the control group keep on treating their employees according to CAU. Follow-up questionnaires are send to the employee at 3, 6, and 12 months. At these points in time, administrative data on cumulative sickness absence days are also collected by means of the registry system of the OHS.

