The collaborating OHS serves approximately one million insured employees. A total of 350 OPs is working for this OHS and each OP serves around 2500 to 3000 employees. Of these employees it is estimated that 1.3% (30% of the national sickness absence rate among Dutch employees of 4.3%) will be on sickness absence because of a CMD during a 1 year period [31]. Therefore, an OP will see around 32 to 39 employees per year who are absent because of CMDs. Following this, the source population of the OHS is large enough to recruit the required number of OPs and employees according to the sample size calculation.

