### Randomisation and treatment allocation

Employees can not be randomly assigned to OPs trained in the intervention or OPs not trained in the intervention because the OPs and employees are bound to each other by the company. It is also impossible to train all OPs and to let them randomly apply the intervention or CAU to employees because of the risk of contamination. Therefore, randomisation occurs at the level of the OP. OPs who have given their consent to participate in the study are randomly assigned to the intervention group or the control group. To ensure a good contrast between these two groups, OPs in the intervention group are specifically asked not to talk about the intervention with OPs in the control group. Additionally, the OPs in the intervention group have two feedback meetings to discuss the application of the intervention with each other.

A computerised random allocation sequence for randomising the OPs is developed by an independent researcher. When all OPs are recruited, the independent researcher, who is blind to the identity of the OPs, uses the allocation sequence to randomise the OPs. After this, the allocation of the OPs can not be changed and the independent researcher informs the researchers about the allocation of the OPs. The allocation of employees follows from the allocation of their OP. Employees with an OP in the intervention group are automatically allocated to the intervention group and employees with an OP in the control group are automatically allocated to the control group.

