### Blinding

Validity can be threatened if employees in the intervention and control group would know about the other group. Because this study is a pre-randomised trial, in which the employees are already randomised before informed consent is given, different information about the study can be provided to the intervention and control group [32]. To ensure that employees are not aware and stay unaware of the two study conditions, the OPs are requested not to talk about this with the employees. Whereas employees are blinded for treatment allocation, blinding of allocation for OPs is not possible because they will know if they are trained in the intervention or not.

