A limitation of the study is the inclusion of participants by the OPs. The possibility exists that OPs in both study groups select those employees who have, in their view, good potential for fast recovery and small chances for a relapse of sickness absence. Although it has been stressed to all OPs to invite all employees eligible for the study, we can not exclude the possibility of bias. Questions to investigate if participating employees were thought to be more suitable for the study are included in the process evaluation for OPs. Another possibility for bias to occur is the selection of employees who have a good relationship with their OP. Unfortunately, we can not exclude this bias, but we ask questions in the process evaluation on the relationship between the OP and the employee. Finally, recruiting 500 employees for the study is a challenge. Most studies in this field have problems with recruiting participants. We have tried to minimise these problems by embedding this study in one large OHS. All participating OPs work for the same OHS and are stimulated to contribute to the study by this OHS. Moreover, we expect fewer refusals to participate because OPs invite employees to participate in the study. The OP has already built a relationship with the employee which will contribute to a safe environment to make the choice to participate in the study.

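### Employees are screened and invited after randomisation by occupational physicians who know their own arm, and the planned safeguards cannot reliably detect or correct selection that differs between arms

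*Protocol article*

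**What the plan says.** The article fixes the order of events.

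- **Randomisation comes first.** Under Randomisation and treatment allocation, OPs are randomised once all have been recruited, and then "the independent researcher informs the researchers about the allocation of the OPs". The Blinding section confirms that "employees are already randomised before informed consent is given".
- **OPs know their arm.** The Blinding section states that "blinding of allocation for OPs is not possible because they will know if they are trained in the intervention or not".
- **The same OPs screen and invite.** Under Study design, "OPs will invite an employee to participate in the study". Under Procedure, "Employees are recruited by the OPs participating in the study. The OP checks all inclusion and exclusion criteria".
- **A researcher makes the contact call.** Procedure has the researcher contact the employee after the OP passes on the details. The Blinding section also allows the two arms to be given different study information.

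The article names one selection risk, under Methodological considerations: "The possibility exists that OPs in both study groups select those employees who have, in their view, good potential for fast recovery". Against it the article sets an instruction to OPs to invite everyone eligible, and process-evaluation questions on suitability and on the OP–employee relationship. Separately, Prognostic measures lists a broad set of baseline variables. Statistical analyses plans a comparison of baseline characteristics, with adjustment for those that differ significantly.

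**The concern.** Randomising OPs makes the OPs comparable. It makes the enrolled employees comparable only if enrolment does not depend on the arm. Here the person who decides on eligibility and invitation knows the arm, and some criteria need judgement, for example whether somatic complaints dominate the work disability.

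The two arms also ask different things of an OP. Enrolling an employee commits an intervention OP to the five-step guidance, while a control OP carries on as before. That the two groups of OPs might choose differently is an inference, but a plausible one.

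The distinction the article misses is this. Selection that is equal in both arms limits how far the result generalises. Selection that differs by arm biases the comparison of recurrent absence days. Intention-to-treat analysis of the enrolled employees does not remove that bias, and neither does the multilevel model. The article discusses only the first kind and presents pre-randomisation as a strength.

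**Working it through.** **1. Sequence.** Randomise OPs, inform the research team, train the intervention OPs, then screen, invite, call and obtain consent. Every step that decides who enters the trial follows allocation and is taken by someone who knows it, or who belongs to the team told it. The article describes no identification of employees before randomisation and no eligibility check by someone unaware of the arm. The one element that may predate allocation is the diagnosis, which is coded at the start of absence. For some early participants it will, but the eligibility check and the invitation do not.

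**2. The plan's own figures (Sample size).**

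- Effect size: 0.25 / 1.4 = 0.179, stated as 0.18.
- Correlation: 0.18 / √(0.18² + 4) = 0.090, stated as 0.09.
- Size: 50 OPs × 5 employees = 250 per group. No power is stated, so this number cannot be reproduced formally.

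**3. Standard error.** With ICC = 0.05 and 5 employees per OP, the design effect is 1 + (5 − 1) × 0.05 = 1.2. In SD units the standard error of the difference between arms is √(2 × 1.2 / 250) = 0.098.

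**4. Illustration: no treatment effect, but selection shifts the arm means by b SD.** The values of b are assumed; the documents give none. The two-sided rejection probability at 5% is Φ(b/SE − 1.96) + Φ(−b/SE − 1.96).

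| Assumed b (SD) | Share of the 0.18 target | b/SE | Rejection probability |
|---|---|---|---|
| 0 | 0 | 0 | 5% |
| 0.05 | 28% | 0.51 | 8% |
| 0.09 | 50% | 0.92 | 15% |
| 0.18 | 100% | 1.84 | 45% |

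A bias in the other direction would hide a real effect in the same way.

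**5. How often the baseline rule would react.** This is the power of a two-sided 5% test on a baseline variable, 250 per arm. The first figure assumes an ICC of 0.05 for that variable (SE 0.098), the second an ICC of 0 (SE √(2/250) = 0.089).

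- Imbalance of 0.18 SD: flagged 45% to 52% of the time.
- Imbalance of 0.09 SD: flagged 15% to 17% of the time.

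These are imbalances in the baseline variable, not in the outcome. If selection works through one measured variable with an assumed correlation of 0.5 with the outcome, a 0.09 SD bias in the outcome needs 0.09 / 0.5 = 0.18 SD in that variable, which is still missed about half the time. A more weakly related variable would have to be more imbalanced and would be flagged more often. Selection on an OP's unrecorded view of relapse risk might not show in any variable.

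**6. The process questions.** They ask the selecting OPs for opinions about employees who took part. The article describes no comparison with eligible employees who were not invited, which is the comparison that would show selection directly.

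**The case against.** Several points on the other side stand.

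- **The article is open about OP selection.** It concedes that bias cannot be excluded, justifies randomising OPs, and makes no false statement here. This is a weakness of design, not an error of fact.
- **The process questions are not worthless.** A reader might infer that they cannot detect differential selection at all. The documents do not support that: the 3-month questionnaire goes to OPs in both arms, so answers could be compared by arm, and the items are not shown. What is supported is that they cannot do so reliably.
- **Baseline data and adjustment are planned.** The prognostic set is wide and includes expectancy to stay at work. The weakness is the rule that adjusts only for what tests as significant.
- **The pool is not a measure of selection.** The article says "an OP will see around 32 to 39 employees per year who are absent because of CMDs". A reader might divide 5 by 39 and by 32 and conclude that OPs pick 13% to 16%. But the denominator is all absentees before the eligibility criteria are applied, and the numerator is those who consented. The share of eligible employees invited is unknown.
- **A translation into days is not supported.** One might assume 20% relapse and 68.5 days per relapse, giving 0.20 × 68.5 = 13.7 days, and note that 16% relapse gives 2.7 days fewer with no treatment effect. The article's stated target is 12.7 days per employee. In that model, selection alone would need relapse to fall to 0.20 − 12.7/68.5 = about 1.5%.
- **Not every criterion is the OP's to shape.** A reader might infer that the OP partly sets the planned return. No section says so, and Study context places responsibility for return on employer and employee.

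It can also be said that screening logs belong in the full protocol. That is fair for the log itself. It does not answer the point, which concerns a recruitment procedure that the article sets out step by step.

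**Conclusion.** The point holds in this form: recruitment after randomisation by unblinded OPs allows the arms to differ in relapse risk, the article does not name that risk, and its safeguards cannot reliably detect or correct it. It bears on the primary comparison and cannot be fully repaired from data on enrolled employees alone.

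The direction and size of any bias are unknown. The figure of about 15% is an illustration. It rests on an assumed 0.09 SD selection difference, the article's ICC of 0.05, 250 analysed per arm without loss, and a normal approximation on the log scale used for planning. A reader might infer that bias has been shown or that its sign is known; the documents support neither.

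**What to change.** 1. Have the registry of the occupational health service, already used for planning and follow-up, generate by the same rule in both arms a list of each randomised OP's employees who meet the objective criteria: age, CMD code, spell length, and no CMD spell in the prior three months.
2. The OP then applies the remaining criteria, including the planned return within two weeks, and records a coded reason for each listed employee not invited.
3. Report enrolled over listed by arm, and compare enrolled with non-enrolled listed employees by arm on registry variables.
4. Adjust the primary analysis for prognostic baseline variables named in advance, instead of those found significant. The variables are already collected.
5. Under Methodological considerations, name selection that differs by arm as a separate risk.
6. Where existing staff allow, have the contact call made by a team member not told the allocation.

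An analysis of registry absence days in all listed employees is at most supportive. If only 13% to 16% were enrolled, a 20% reduction would shrink to about 0.20 × 0.13 = 2.6% to 0.20 × 0.16 = 3.2%. The listed pool is smaller than all CMD absentees, so dilution would be somewhat less, but still strong.

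Cost: a periodic registry query, a short code per non-invited employee, and one extra table. The list will include employees not yet near a planned return, which adds some OP administration. A caller unaware of allocation may need extra staff and must fit with the arm-specific study information that the Blinding section allows.

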#### Treatment of participants in the intervention group

The intervention consists of five steps the employee has to undertake when return-to-work is started. The OP monitors that the employee follows these steps and uses interventions to activate the employee when needed. The five steps are delineated below.

1. Make an inventory of problems and/or opportunities encountered at work

2. Brainstorm on solutions

3. Write down the solutions and the support needed and assess the applicability

4. Discuss the solutions with the line manager and make an action plan

5. Evaluate the action plan and the implementation of solutions

The OP can use assignments for the employee to write down and structure the process. In general, the OP will counsel on the process level. (S)he does not discuss the content of problems and solutions but challenges the employee to reflect on the relative seriousness of problems and the feasibility of solutions. This can be done by asking questions that stimulate the employee to think about possible perspectives. This form of guidance is related to Socratic questioning. The intervention differs from the guideline of the Netherlands Society of Occupational Medicine by the emphasis on problems and possibilities encountered *at work *when an employee has already returned to work.

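### Employees consent after allocation, on information that may differ by arm, so who accepts can depend on the arm even if every OP invites all eligible employees

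*Protocol article*

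**What the plan says.** Randomisation and treatment allocation: OPs are randomised together once recruited ("When all OPs are recruited, the independent researcher, who is blind to the identity of the OPs, uses the allocation sequence to randomise the OPs"), and "The allocation of employees follows from the allocation of their OP".

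Blinding: the trial is called pre-randomised, meaning that "the employees are already randomised before informed consent is given". The protocol uses this order so that "different information about the study can be provided to the intervention and control group", with the aim that employees stay unaware of the two conditions. For OPs, "blinding of allocation for OPs is not possible because they will know if they are trained in the intervention or not".

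Procedure: the OP checks eligibility and "hands over an information folder about the study". With the employee's approval the OP passes on contact details, the researcher calls, and the consent form and baseline questionnaire are sent together. The intervention OP may start only "When the informed consent and the baseline questionnaire are filled in and returned to the researcher".

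Treatment of participants in the intervention group: step 4 of the five steps is "Discuss the solutions with the line manager and make an action plan".

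Process evaluation measures: intervention employees, but not controls, have a baseline questionnaire with items on their readiness for change in relation to the intervention.

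**The concern.** Random allocation of OPs makes the two pools of eligible employees comparable. The trial analyses only those who accept, and acceptance comes after allocation. If the two arms are offered differently described studies, the reasons for saying yes or no can differ. For example, an employee in conflict with a line manager might weigh an offer that mentions a talk with that manager differently from an offer that does not.

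The enrolled groups could then differ in relapse risk before any treatment is given. Intention-to-treat analysis protects comparability from enrolment onwards and cannot restore what was lost before it. Baseline answers are exposed to the same problem, because they are given after the employee has read the arm's material.

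**Working it through.** **Order of events.** (1) All OPs are allocated. (2) The employee's arm follows from the OP. (3) An OP who knows the arm hands over the folder. (4) The employee agrees or declines to be contacted. (5) The employee agrees or declines on the telephone. (6) The employee returns consent and baseline, or does not. Steps 4 to 6 are the employee's own decisions, and all follow allocation.

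**Does the information differ?** The Blinding section says only that it can. The intervention-only baseline items on readiness for change suggest that it does, since they are hard to answer without knowing of the intervention.

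**Which safeguards reach this step?**
- Methodological considerations: OPs are urged to invite everyone eligible. This acts on invitation, before steps 4 to 6.
- Process evaluation: questions to OPs on the suitability of participants, and questions on the OP-employee relationship. These describe those who joined.
- Statistical analyses: adjustment for baseline differences that turn out significant. This leaves out non-significant and unmeasured grounds for refusing, and refusers return no baseline questionnaire.

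**Illustration 1 (assumed consent rates and risks).** The documents give no consent rates. The Background section reports that one in five relapses; take 20% as the risk among the 80% assumed to enrol in the control arm. Let 60% enrol in the intervention arm, so that a further 20% refuse, with relapse risk r. There is no treatment effect.

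Enrolled intervention risk = (0.80 × 0.20 − 0.20 × r) / 0.60

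- r = 0.30 (1.5 times average): (0.16 − 0.06)/0.60 = 16.7%, which favours the intervention.
- r = 0.10 (0.5 times average): (0.16 − 0.02)/0.60 = 23.3%, which works against it.
- r = 0.20: (0.16 − 0.04)/0.60 = 20.0%. Unequal consent rates alone do no harm.

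With 70% enrolling in the intervention arm, the first two become (0.16 − 0.03)/0.70 = 18.6% and (0.16 − 0.01)/0.70 = 21.4%. If the same extra employees refuse in both arms, the difference is zero.

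**Illustration 2 (assumed selection model, equal participation rates).** Let X be a standard normal prognosis score. In one arm only, participation is p(X) = 1/(1 + exp(−(a + bX))), with b the log odds ratio per SD of X and a set to give the chosen rate. The mean among participants is E[X p(X)]/E[p(X)]. For participation of 30% to 70% and odds ratios of 1.1 to 1.5, mean prognosis differs between arms by 0.03 to 0.27 SD. Inverting the odds ratio reverses the sign. If X correlates 0.3 to 0.5 with log absence days, the bias is about 0.01 to 0.14 SD of log days, in either direction (0.0285 × 0.3 = 0.009; 0.2745 × 0.5 = 0.137).

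The yardstick is the trial's own precision, from the Sample size section (50 OPs of five employees per arm, ICC 0.05):
- design effect 1 + (5 − 1) × 0.05 = 1.2
- effective number per arm 250/1.2 = 208.3
- standard error √(2/208.3) = 0.098 SD

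The chance of a false positive at a two-sided 5% level is 1 − Φ(1.96 − bias/0.098) + Φ(−1.96 − bias/0.098). A bias of 0.05, 0.09 or 0.12 SD gives about 8%, 15% or 23%. With the same dependence on prognosis in both arms, the bias is zero and the level stays at 5%.

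**The case against.** The folder, telephone script and consent text are not in the article, and the Study design section says that the ethics board approved the information letters and informed consent. Nothing shows that the control material reads as a mere questionnaire study, or that the intervention material sets out the five steps. This stands: what the employee is told in each arm is unknown.

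Arm-specific information was chosen deliberately to keep employees unaware of a second condition. That aim is legitimate, and concealment does prevent preference for the other arm. It does not prevent unequal acceptance of two differently described offers, and the aim does not require different texts.

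The article is not silent on acceptance. Methodological considerations expects fewer refusals because the OP does the inviting, and lists selection of employees with a good OP relationship without saying who does the selecting. Baseline is collected before the intervention starts, so measured imbalance can be seen. All this stands as partial mitigation, but refusal that differs by arm is not named.

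A reader might infer more than the text supports:
- That employees choose their arm. They cannot; the arm is fixed by the OP, and they only join or refuse.
- That differential refusal occurs, or that it flatters the intervention. The documents show a route for bias and give neither its occurrence nor its sign. Employees who expect trouble at work might accept extra guidance more readily, which would work against the intervention.
- That the relapse percentages can be set against the 20% target. That target is a reduction in recurrent absence days, whereas the Background figure is a proportion relapsing.

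**Conclusion.** The point holds as a structural risk. Consent follows allocation, and the protocol allows the information behind that consent to differ by arm, so acceptance and baseline answers can depend on the arm even with complete invitation. The stated safeguards do not reach this step, or reach it only in part.

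Its direction and size cannot be derived from the documents. The illustrations show only that, on assumed inputs, differential acceptance could shift the comparison either way by an amount that is not negligible beside a standard error of 0.098 SD. They also show that the bias vanishes when acceptance depends on prognosis equally in both arms. Because the remedy is cheap and keeps the blinding aim, it is worth making.

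**What to change.** Replace the arm-specific information with one identical neutral folder, telephone script and consent text in both arms, used until the consent form and baseline questionnaire are returned. The text should describe guidance by the employee's own OP around return-to-work, possibly involving the line manager, and should not mention a second arm. The intervention OP then explains the five steps after the release that the Procedure section already provides for.

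Move the intervention-only employee questionnaire on readiness for change to after that return; otherwise it discloses the intervention at the moment the neutral text is meant to protect.

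Keep employees who later decline the steps in follow-up and in the intention-to-treat analysis. Have OPs log invited and declining employees by arm, because under the Procedure section the researcher receives details only of those who agree to be contacted.

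Cost: revised letters, ethics approval of the neutral wording (including how line-manager involvement is described before consent), a small logging task for OPs, and some refusals that become non-adherence and slightly dilute the estimated effect.
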